## 4. STUDY POPULATION

### 4.1 Population (base)

A total of 40 apparently healthy, untreated (pre)hypertensive men and women will be sourced from the Wageningen population and surroundings. Selection of subjects will be based on the exclusion and inclusion criteria detailed below.

### 4.2 Inclusion criteria

Both men and women will be accepted onto the study providing they are between the ages of 30 and 80 and have a systolic blood pressure between 125 and 160 mmHg and Body Mass Index (BMI) score between 20 and 40 kg/m^2. All subjects must meet the inclusion and not meet the exclusion criteria (see tables 4.1 and 4.2 respectively).

Table 4.1. Inclusion criteria for short-term flavonoid study.

| Inclusion Criteria                                                                                                                                                                                                                                                                                                                                                                                                                                                                                                                                                                                                                                                                                                                         |
|--------------------------------------------------------------------------------------------------------------------------------------------------------------------------------------------------------------------------------------------------------------------------------------------------------------------------------------------------------------------------------------------------------------------------------------------------------------------------------------------------------------------------------------------------------------------------------------------------------------------------------------------------------------------------------------------------------------------------------------------|
| 
 
• Systolic Blood Pressure between 125 and 160 mmHg
 
• Age between 30 and 80 years
 
• BMI > 20 and ≤ 40
 
• Apparently healthy:               
 
- No reported current or previous metabolic diseases
 
- No history of cardiovascular diseases
 
- No history of renal, liver or thyroid diseases
 
- No history of gastrointestinal diseases
 
- No diabetes mellitus
 
- Fasting laboratory parameters within normal range: complete blood count (RBC, WBC, PLT, HB, HT), renal function (serum creatinine, ureum), liver function (ALAT, ASAT, γ-GT), and serum glucose.
 
 
 
 |

### 4.3 Exclusion criteria

*Before the start of the study:*

Subjects who do not meet the inclusion criteria or who have one or more of the exclusion criteria before the start of the study will be deemed ineligible and will be excluded from taking part. See table 4.2 for an overview of the exclusion criteria.

*During the intervention:*

Subjects who experience a serious adverse event, such as hospitalisation, will be removed from the study. For a definition of a serious adverse event, see chapter 7.2. In addition, subjects whose systolic blood pressure rises above 160 mmHg during the intervention period will be informed of their blood pressure reading and the study physician will contact the subject's General Practitioner (GP). These subjects will be removed from the study if the GP deems it necessary. If the GP decides to prescribe blood pressure-lowering medication then these subjects will also be removed from the study.

Table 4.2. Exclusion criteria for short-term flavonoid study.

| Exclusion Criteria                                                                                                                                                                                                                                                                                                                                                                                                                                                                                                                                                                                                                                                                                                                                                                                                                                                                                                                                                                                                                                                                                                                                                                                                                                                                                                                                                                                                                                                                                                                                                                                                                                                                                                                                                                                                                                                                                                                                           |
|--------------------------------------------------------------------------------------------------------------------------------------------------------------------------------------------------------------------------------------------------------------------------------------------------------------------------------------------------------------------------------------------------------------------------------------------------------------------------------------------------------------------------------------------------------------------------------------------------------------------------------------------------------------------------------------------------------------------------------------------------------------------------------------------------------------------------------------------------------------------------------------------------------------------------------------------------------------------------------------------------------------------------------------------------------------------------------------------------------------------------------------------------------------------------------------------------------------------------------------------------------------------------------------------------------------------------------------------------------------------------------------------------------------------------------------------------------------------------------------------------------------------------------------------------------------------------------------------------------------------------------------------------------------------------------------------------------------------------------------------------------------------------------------------------------------------------------------------------------------------------------------------------------------------------------------------------------------|
| 
 
• Body mass index > 40 and ≤20
 
• Secondary hypertension
 
• Weight loss or weight gain of 5 kg or more during the last 2 months
 
• Usage of non-steroidal anti-inflammatory drugs (acetylsalicylic acid, ibuprofen, naproxen) and not able or willing to stop taking them from at least 4 weeks prior to the study
 
• Usage of cholesterol-lowering medication
 
• Daily usage of corticosteroids
 
• Medical treatment that may affect blood pressure and not able (or willing) to stop
 
• Taking nutritional supplements and unwilling to discontinue
 
• Lactating, pregnant or intend to become pregnant during study
 
• Reported dietary habits: medically prescribed diet, slimming diet;
 
• Reported average alcohol consumption > 2 glasses/d (men) or >1 glass/d (women)
 
• Problems with consuming the supplements or following the study guidelines
 
• Unwilling to undergo home or office blood pressure measurements
 
• Recent blood donation i.e. 1 month (male subjects) or 2 months (female subjects) prior to the study and planned donation during the study period
 
• Reported intense sporting activities > 10 h/w
 
• Not agreeing to be informed about unexpected and medically relevant personal test-results, or not agreeing that their general practitioner will be informed about these results
 
• Participation in another biomedical trial less than 2 months before the start of the study or at the same time
 
• No signed informed consent form
 
• Clinical disorders that could interfere with the intervention
 
• Unable to comply with the study procedure (e.g. holidays, urine collection, blood sampling)
 
• Smokers
 
• Difficulty imaging brachial artery by ultrasonography
 
 |

#### 4.4 Sample size calculation

With FMD as the primary endpoint, a calculation was carried out to determine optimal sample size for the trial. To date, no studies have been conducted investigating the effects of pure flavonoid supplements in doses proposed for this study. For this reason, the sample size calculation will be based on results from studies conducted using cocoa containing an equivalent amount of epicatechin. Based on these previous studies, a standard deviation of the treatment response of 2.7 is assumed for FMD [23, 25].

Studies investigating the acute effects of cocoa consumption report an increase in FMD of approximately 1.5% – which will be used as the expected effect size for the acute effects of the cocoa intervention. Assuming a power of 0.80 and  $\alpha=0.025$ , and based on a crossover intervention design with multiple testing, 25 subjects would be required to identify a change in FMD of 1.5%. Assuming a dropout rate of approximately 10%, the optimal sample size to investigate the acute effects of flavanol-rich cocoa is 30.

Studies investigating the chronic effects of cocoa consumption report an increase in FMD of approximately 1.3% – which will be used as the expected effect size for the chronic effects of the intervention. Assuming a power of 0.80 and  $\alpha=0.025$ , and based on a crossover intervention design with multiple testing, 35 subjects would be required to identify a change in FMD of 1.3%. Assuming a dropout rate of approximately 10%, the optimal sample size to investigate the chronic effects is 40.

The following formula was used to calculate sample size:

|                                               |                                                                                                                                                       |
|-----------------------------------------------|-------------------------------------------------------------------------------------------------------------------------------------------------------|
| $n = 7.9 \times (SD_{\text{response}} / D)^2$ | $n$ = sample size
$SD_{\text{response}}$ = expected standard deviation of the response to treatment
$D$ = expected effect size due to treatment |
|-----------------------------------------------|-------------------------------------------------------------------------------------------------------------------------------------------------------|

Figure 4.1. Equation used to calculate sample size.

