## 8. STATISTICAL ANALYSIS

Statistical analyses will be conducted based on the intention-to-treat principle. An additional per-protocol analysis will be conducted, however, the intention-to-treat analysis will remain leading. Researchers involved in the statistical analysis will remain blinded to treatment allocation. For statistical significance, a two-tailed p-value of 0.05 will be set.

All data collected during the study will be quantitative. Continuous variables will be expressed as means  $\pm$  standard deviation while categorical variables will be expressed in frequencies. Data will be tested for normality by visual inspection of Q-Q plots and histograms.

Basic descriptive analyses (including age, gender, BMI and blood pressure) will be carried out based on subject characteristics obtained during the screening and baseline measurements.

A repeated measures analysis of variance (ANOVA) will be conducted to compare differences in intraindividual responses to the treatments. Changes from  $T_0$  to  $T_1$  will be used to determine the chronic effect of the intervention. Changes from  $T_1$  to  $T_A$  will be used to determine the acute effects of the intervention. Additional paired t-tests will be carried out to compare baseline values ( $T_0$ ) of outcome measures.

For data that are not normally distributed, a nonparametric Friedman's rank test will be conducted. All statistical analyses will be carried out using the SPSS 19.0 or SAS 9.2 software packages.

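### Section 4.4 claims 80% power at α=0.025 with allowance for multiple testing, but its multiplier of 7.9 belongs to two-sided α=0.05, so the adjustment is in neither the formula nor Section 8

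*Protocol*

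**What the plan says.** Section 4.4 of the protocol sizes the trial on flow-mediated dilation (FMD), the primary endpoint, with an assumed SD of the treatment response of 2.7.

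- **Chronic effect.** Cocoa studies "report an increase in FMD of approximately 1.3"%, which becomes the expected effect. "Assuming a power of 0.80" and α=0.025, the section states that, "based on a crossover intervention design with multiple testing, 35 subjects would be required to identify a change in FMD of 1.3"%. Allowing about 10% dropout, it sets 40.
- **Acute cocoa effect.** The same power and α are used. The cited studies "report an increase in FMD of approximately 1.5"%, and "25 subjects would be required to identify a change in FMD of 1.5"%. With dropout this becomes 30.
- **Formula.** Figure 4.1 gives the only equation: "n = 7.9 \times (SD_{\text{response}} / D)^2". Here D is the expected effect and the SD is described only as that of the response to treatment.

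Section 4.4 does not say whether 0.025 is one-sided or two-sided. Section 8 gives the only testing threshold in the protocol: "For statistical significance, a two-tailed p-value of 0.05 will be set". It mentions neither 0.025 nor an adjustment for two active arms.

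**The concern.** With two active arms each compared with placebo, an α of 0.025 tied to multiple testing reads as 0.05 divided by two. A sample size that honours it should carry the larger critical value, and the multiplier 7.9 does not. The power, the α and the number of subjects stated for the primary endpoint therefore cannot all be true together.

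The consequence depends on which α is finally applied. If each comparison is tested at 0.025, a null result would be read as having had an 80% chance of detecting a 1.3-point effect when the chance was nearer 70%. If each is tested at 0.05, as Section 8 implies, the power is about right, but the control of multiplicity that Section 4.4 advertises does not exist.

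**Working it through.** **Inputs, all from the protocol.** SD 2.7; D = 1.3 (chronic) and 1.5 (acute cocoa); power 0.80; α = 0.025; multiplier 7.9; dropout about 10% (Section 4.4). Two-tailed tests at 0.05 (Section 8).

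**1. Reproduce the protocol's figures with its own formula.**
- Chronic: 7.9 × (2.7/1.3)² = 34.1, which rounds up to the stated 35.
- Acute: 7.9 × (2.7/1.5)² = 25.6. The protocol states 25; rounding up gives 26.

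The stated numbers therefore come from 7.9.

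**2. Identify the multiplier, (z for α + z for power)², at 80% power.**

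| α | Calculation | Multiplier |
|---|---|---|
| two-sided 0.05 | (1.960+0.842)² | 7.85 |
| one-sided 0.025 | (1.960+0.842)² | 7.85 |
| two-sided 0.025 | (2.241+0.842)² | 9.51 |

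The 7.9 is the first or second row, not the third.

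**3. Completers needed at two-sided 0.025.** By normal approximation, 9.505 × (2.7/1.3)² = 41.0. A paired t calculation (noncentral t, n−1 degrees of freedom) needs 44. Section 4.4 states 35, and even the full enrolment of 40 falls short.

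**4. Power for D = 1.3, SD = 2.7.** The normal approximation is Φ(D√n/SD − z). For n = 36 at two-sided 0.025, 1.3 × 6/2.7 = 2.889 and Φ(2.889 − 2.241) = 0.74. The paired t column uses the noncentral t distribution.

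| Completers | α (two-sided) | Paired t | Normal |
|---|---|---|---|
| 35 | 0.025 | 69% | 73% |
| 36 (40 less 10%) | 0.025 | 71% | 74% |
| 40 (no dropout) | 0.025 | 76% | 79% |
| 35 | 0.05 | 79% | 81% |
| 36 | 0.05 | 80% | 82% |

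Section 8 plans a repeated-measures ANOVA. Using its pooled error degrees of freedom, 2(n−1)−2, the power at 0.025 is 71% for 35 completers and 72% for 36, within the same range.

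**5. Difference detectable with 80% power, 36 completers, two-sided 0.025.** Normal: (2.241+0.842) × 2.7/√36 = 1.39 points. Paired t: 1.44 points. The protocol's target is 1.3.

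**6. Acute cocoa calculation.** The target of 30 less 10% leaves 27, which gives 69% (t) or 74% (normal) at two-sided 0.025. At 0.025, 80% power would need 31 (normal; 30.8 before rounding) to 34 (t) completers.

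**The case against.** **The α of 0.025 may be one-sided.** Section 4.4 is silent on sidedness, and 7.9 fits one-sided 0.025 exactly. This does not rescue the text. One-sided 0.025 has the same critical value as two-sided 0.05, so it carries no allowance for multiple testing, which is what Section 4.4 says it includes. Section 8 is also explicitly two-tailed.

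**The design has its 80% power for the test in Section 8.** This stands. At two-tailed 0.05, 36 completers give 80–82%. A reader might infer that the trial is underpowered for its planned analysis, or that it must enrol more. The protocol does not support that: the shortfall appears only if 0.025 per comparison is the level actually used.

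**The t-correction explains part of the gap.** This also stands. The protocol's formula is a normal approximation, and like for like the power at 0.025 is 73–74%. The 69–71% figures add the small-sample correction, hence the range.

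**The SD may be the wrong one.** The formula is the paired form, so 2.7 should be the SD of the active-minus-placebo difference in change. A reader might infer that 2.7 is a single-arm SD and that power at 0.025 could fall to 39% with 36 completers. That figure requires zero correlation between a subject's changes under the two treatments. Under the same single-arm assumption, a correlation of 0.6 gives an SD of 2.7 × √0.8 = 2.41 and 81% power. In a crossover, the protocol's definition can naturally be read as the within-subject effect. The wording should be clarified, but no loss of power is shown.

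**The rounding of 25.6 to 25 is immaterial.** Agreed. The target of 30 leaves 27 after 10% dropout, which covers 26.

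**Conclusion.** The point holds. Section 4.4 is wrong as written: 80% power, two-sided α=0.025 and 35 completers are incompatible with its own SD and effect, and the stated adjustment for multiple testing is in neither Figure 4.1 nor Section 8. If 0.025 per comparison is intended, the expected completers give roughly 70–74% power and the type II error is about 26–31% across 35 to 36 completers, instead of 20%. If two-tailed 0.05 is intended, the power is sound and the multiplicity claim is what fails.

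This rests on the protocol's SD of 2.7, its effect of 1.3, 10% dropout, and 0.025 being meant as a two-sided level per active-versus-placebo comparison. The mismatch between the claim and the formula does not depend on that last assumption; the size of the power loss does. Because this is the stated power for the primary endpoint and the correction is cheap, it should be made.

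**What to change.** Reconcile Section 4.4 with Section 8 in one of two ways.

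(a) **Keep the adjustment.** Replace 7.9 with 9.5 in Figure 4.1. Drop the 80% claim and restate power for 40 enrolled and 36 completing as about 71–74% for 1.3 points at two-sided 0.025, with a detectable difference of about 1.4 points. Set 0.025 for each active-versus-placebo comparison in Section 8. Restate the acute cocoa figures on the same basis.

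(b) **Drop the adjustment.** State that the calculation gives 80% power for one unadjusted comparison at two-sided 0.05, and remove the claim of α=0.025 with multiple testing. This is the smaller edit and agrees with Section 8 as it stands, but the protocol then no longer claims multiplicity control across the two active arms.

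Under either option, say in one sentence which SD the 2.7 is. If option (b) retains the acute calculation, correct 25 to 26.

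The cost is rewording Section 4.4 and, under (a), one sentence in Section 8. No extra subjects are needed. The price is a less favourable stated power under (a) or a weaker error-control claim under (b).

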## 5. TREATMENT OF SUBJECTS

### 5.1 Investigational product/treatment

The three intervention arms (QUER, EPI, and PLA) will each use different investigational products. During the QUER intervention, participants will be required to take supplements of quercetin-3-glucoside (160mg/d) in the form of capsules. Epicatechin supplements (100mg/d), also in the form of capsules, will be provided during the EPI intervention arm. These dosages are based on three times the 90th percentile of epicatechin and quercetin intake [20, 40]. Finally, capsules containing microcrystal cellulose and 1% colloidal siliciumdioxide will be used as placebo capsules. The flavonoid capsules will also contain microcrystal cellulose as an excipient. To prevent differentiation in appearance, the placebo capsules will be produced by the same company where the flavonoid capsules will be made (*Het Gelre Apotheek, Apeldoorn*). All supplements will be encapsulated in non-transparent capsules and will be matched for appearance and size (capsule size “0”). During the 4-week intervention period, two capsules will be consumed per day - one at the lunch and the second in the evening before dinner. Participants will be asked to consume the capsules with a meal and a glass of water.

Two hours after the follow-up measurements, participants will be asked to consume two additional capsules with a glass of water. This will be done to determine the acute effects of flavonoid supplementation on markers of cardiovascular health.

Four weeks after completion of the last intervention arm, participants will be asked to return to the university on two different mornings – separated by two weeks. Measurements of vascular and endothelial function will be taken before and two hours after consumption of either a high or a low-flavanol cocoa beverage. Consumption of the low or high-flavanol cocoa will be randomly assigned. The high-flavanol cocoa beverage will be matched such that it provides the same amount of epicatechin as the daily dose of epicatechin during the intervention (i.e. 100mg).

During the study, participants will be provided with a list of high-flavonoid containing foods (see Appendix I). They will be asked to avoid over-consumption of such food products during the intervention period. Specifically, participants will be asked to consume no more than 1 cup of tea or glass of red wine per day and to avoid the consumption of chocolate, apples and onion soup.

## 6. METHODS

### 6.1 Study parameters/endpoints

#### 6.1.1 *Main study parameter/endpoint*

The main study parameter is the percentage change in FMD before and after the intervention period.

#### 6.1.2 *Secondary study parameters/endpoints*

Secondary study parameters include;

- Changes in blood pressure as measured by systolic, diastolic, central and 24-hour blood pressure.
- Changes in macrovascular function as measured by PWA and PWV as well as microvascular function as measured by vasomotion.
- Changes in biomarkers of vascular function as assessed by concentrations of Nitric Oxide, endothelin-1 and ADMA etc.
- Changes in biomarkers of endothelial function as assessed by measurement of plasma levels sVCAM-1, sICAM-1, sE-selectin etc.
- Changes in biomarkers of inflammation as assessed by measurement of plasma levels of CRP, IL-6, IL-8, TNF- $\alpha$  etc.
- Changes in PBMC gene expression as a measurement of gene expression of inflammation.
- Changes in renal function as estimated from glomerular filtration rate (GFR) using serum creatinine.
- Changes in markers that affect vascular function as measured by plasma concentrations of lipoproteins.
- Changes in insulin resistance as measured using HOMA-IR through plasma insulin and glucose levels.

